Our primary objective is to test the efficacy of a pharmacological intervention in reducing delirium severity and duration among adults cared for in the ICU. Our primary hypothesis is that, in comparison to usual care, intervention patients will have (1) reduced delirium severity at one week following randomization or hospital discharge, and (2) fewer hospital days with delirium or coma. The secondary hypothesis theorizes that the study intervention will result in (1) shorter hospital lengths of stay, (2) lower ICU, hospital, and 30-day mortality, and (3) lower hospital-acquired complications related to delirium.

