### Planned Analysis

#### Data Analysis

We will conduct intention-to-treat analyses to test the intervention effects on the primary outcomes. No interim analysis is planned for early termination due to efficacy. To formally test for potential harm due to the intervention, 3 interim analyses will be performed using the proposed primary analysis methods after the completion of 0.25, 0.5 and 0.75 of the projected 428 evaluable subjects, using the O'Brien-Fleming boundary, for an overall significance level of 0.05 at study completion.

To test the intervention effect on severity of delirium, we will use the primary outcome of DRS-R-98 severity score on day 8 post-randomization. The primary analysis to test the intervention effect on day-8 DRS-R-98 severity score will be analysis-of-covariance (ANCOVA) with the baseline score as a covariate, after testing and removing any intervention-by-baseline score interaction. If there is a significant interaction, we will test the intervention effect at the mean of the baseline DRS-R-98 severity score. We will use the last observed DRS-R-98 forward to Day 8 as the primary outcome in one analysis. For sensitivity analyses, we will use different methods to impute the missing data. For example, we will impute the missing Day 8 DRS-R-98 severity scores with their worst score on record for patients who have been discharged with delirium or died before day 8. For patients who were hospitalized but could not be evaluated for whatever reason on day 8, we could also interpolate their previous and subsequent DRS-R-98 severity scores to estimate the missing Day 8 score.

We will also test the intervention effect on the repeated measures of DRS-R-98 severity scores using a mixed-effects model. An appropriate contrast for the day 8 effect will be used to corroborate the results of the ANCOVA in the primary analyses. This analysis will provide additional information on the time course of the severity of delirium from its onset in the ICU, with or without intervention.

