To test the intervention effect on duration of delirium, we will compare between groups the number of coma-free and delirium-free days in the first 8 days post-randomization using a two-sample t-test corroborated with the Wilcoxon rank sum test. The intervention effect will be further tested while controlling for patient characteristics using multiple regression. Patients who die before day 8 will have all subsequent days counted as not coma-free or delirium-free. We will impute all days post-discharge as coma-free and delirium-free.

For secondary outcomes, binary measures, e.g. mortality and complications, logistic regression will be used to test the intervention effect, controlling for covariates when appropriate. Highly skewed outcomes such as hospital and ICU length of stay will be compared between groups using nonparametric tests, such as Wilcoxon's rank sum test, and semiparametric survival analyses which can control for covariates.

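### Carrying the last DRS-R-98 score forward to day 8 for patients discharged alive biases the severity comparison against the arm that leaves sooner, if scores are still falling at discharge

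*Protocol article*

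**What the plan says.** All of the following is in the Protocol article.

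- **Endpoint, Data Analysis:** "we will use the primary outcome of DRS-R-98 severity score on day 8 post-randomization", analysed by ANCOVA with the baseline score as covariate.
- **Endpoint, Background (hypotheses):** "reduced delirium severity at one week following randomization or hospital discharge".
- **Missing day-8 scores:** "We will use the last observed DRS-R-98 forward to Day 8 as the primary outcome in one analysis". Discharge alive, death and a missed assessment are not distinguished.
- **Named sensitivity rule for patients who have left:** "their worst score on record for patients who have been discharged with delirium or died before day 8". Interpolation is mentioned only for patients still in hospital.
- **Mixed-effects model on the repeated scores:** "An appropriate contrast for the day 8 effect will be used to corroborate the results of the ANCOVA in the primary analyses".
- **Duration primary:** "We will impute all days post-discharge as coma-free and delirium-free".
- **Secondary hypothesis for the intervention (Background):** "shorter hospital lengths of stay".
- **Harm monitoring:** "3 interim analyses will be performed using the proposed primary analysis methods", with O'Brien-Fleming boundaries at one quarter, one half and three quarters of 428 evaluable subjects.

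The Primary Outcome section has RASS and CAM-ICU assessments running until hospital discharge. The article describes no DRS-R-98 rating after that point.

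**The concern.** A patient discharged on day 4 has no day-8 score, so the day-4 score stands in for it. If that patient was still improving, the substitute is too high. When both arms discharge at the same pace, the error is about equal and largely cancels from the comparison. The trial, however, hopes that the intervention shortens stay. Intervention scores would then be frozen earlier, and so higher, than control scores, and the error runs against the arm expected to do well.

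Two things are at stake. A real severity benefit is diluted. And an intervention that only speeds discharge can look harmful, in a test that is also used for the formal harm looks on which the data safety monitoring board may recommend stopping.

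The text is also not aligned with itself. The hypothesis allows the score at discharge as the endpoint, whereas the analysis names day 8. For a patient who leaves while delirious, severity holds a delirious score up to day 8, while duration counts those same days as free of delirium.

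**Working it through.** **Inputs from the article.** 428 evaluable subjects, 1:1 (214 per arm); severity score 0 to 39, higher is worse; overall level 0.05, sidedness not stated; three harm looks before the final analysis. The article gives no hospital stay, DRS-R-98 trajectory, SD, effect size or power, so 428 cannot be rebuilt. For scale only: with 214 per arm and two-sided 0.05, the detectable standardized effect is (1.96 + 0.84) × √(2/214) = 0.27 SD at 80% power, and (1.96 + 1.28) × √(2/214) = 0.31 SD at 90%.

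**Assumed inputs.** Baseline 20 (SD 6), daily noise SD 3, falls of 0.5 to 2 points per day that continue after discharge, exponential stay with control mean 8 days, identical true trajectories in both arms. Only discharge timing differs.

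**Step 1, closed form.** If scores fall r points per day and discharge is unrelated to the score, then

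bias ≈ r × (mean day of last score, control − mean day of last score, intervention).

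For stays rounded up to whole days and capped at day 8, the mean day of the last score is the sum of exp(−k/m) over k = 0 to 7, where m is the mean stay. This gives 5.38 for m = 8, 5.12 for m = 7 and 4.80 for m = 6. The gap is 0.26 days for a stay one day shorter and 0.58 days for two days shorter.

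**Step 2, simulation of the stated ANCOVA with carry-forward** (positive = intervention looks worse; 600 trials per row):

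| Fall per day | Mean stay 8 v 7: closed form / simulated | Mean stay 8 v 6: closed form / simulated | False harm (z > 1.96), 8 v 6 |
|---|---|---|---|
| 0.5 | +0.13 / +0.14 | +0.29 / +0.31 | 14% |
| 1.0 | +0.26 / +0.28 | +0.58 / +0.57 | 25% |
| 1.5 | +0.39 / +0.35 | +0.87 / +0.83 | 34% |
| 2.0 | +0.53 / +0.45 | +1.17 / +1.00 | 39% |

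With mean stays of 8 and 6 days, 58% and 69% leave before day 8. The nominal false-harm rate is 2.5%. The true day-8 difference in these runs is −0.03 to +0.03. With equal stays the artefact is −0.03 to +0.02 and false harm 2.5% to 3.0%. The simulated values fall below the closed form at steep falls, where scores reach the floor.

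**Step 3, where the bias fades.**

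- Discharge only once the score is below 10, faster in the intervention arm: +0.32, false harm 14%.
- Discharge only once the score is below 5: +0.02, false harm 4%.
- Scores flat after discharge (fall of 1 per day until then, 8 v 6 days): carry-forward +0.56, true difference +0.56, so no bias.

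**Step 4, a working intervention.** In a separate simulation (fall of 1.2 points per day continuing after discharge, discharge depending on the current score), a true day-8 effect of about −1.9 points came out as −1.34 under carry-forward, an attenuation of (1.9 − 1.34)/1.9 ≈ 30%. Power was 80%, against 93% for a mixed model fitted with known covariance.

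**Step 5, the harm looks.** Two-sided O'Brien-Fleming bounds for four equal looks at 0.05 are |z| = 4.05, 2.86, 2.34 and about 2.02. A 25% rate at 1.96 implies a final drift of 1.96 − 0.674 = 1.286. At information fraction t the mean z is 1.286 × √t, that is 0.643, 0.909 and 1.114. The marginal chance of crossing in the harm direction is then about 0.03%, 2.6% and 11% at the three looks. Without the artefact it is about 0.003%, 0.2% and 1.0%.

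**The case against.** The best defence is the hypothesis itself. It places severity at one week or at hospital discharge, and for an early leaver the last score roughly is the discharge score. Carry-forward then implements the endpoint rather than imputing it. This stands in part. But the analysis section names day 8, and the mixed-model contrast is also set at day 8, so the two statements need reconciling. A discharge-time score would still compare the arms at different times if treatment changes discharge.

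Second, the plan already has other analyses: carry-forward is introduced as one analysis, the sensitivity methods are given as examples, and the mixed model is prespecified. That softens the point. It does not remove it, because the only named rule for discharged patients substitutes their worst score, which can only move scores upward, and the mixed model is limited to corroboration.

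Third, the mixed model is not better under every assumption. In a simulation with 63% versus 51% out before day 8 and a continuing fall of 1.2 points per day, the true difference was about 0, carry-forward gave +0.71 and the mixed model 0.00. With scores flat after discharge, the true difference was +0.82, carry-forward gave +0.76 and the mixed model +0.01. The ranking reverses. This stands, and it is why carry-forward should be kept as a sensitivity analysis.

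Three stronger readings are tempting and are not supported:

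- That any difference in length of stay biases the result. Scores must also go on changing after discharge.
- That the two primaries contradict each other for every discharged patient. A patient who leaves without delirium carries a low score and is counted delirium-free, which is consistent. The conflict is confined to those discharged with delirium.
- That Table 1 shows about 30% of trial patients leaving early: (228 × 0.38 + 67 × 0.14 + 40 × 0.12)/335 = 0.30. That share describes all ICU admissions, 68% of them (228/335) to the progressive unit, not enrolled delirious patients. The table also gives ICU stay, not hospital stay.

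**Conclusion.** The point holds in a conditional form. Carry-forward for live discharges biases the day-8 severity contrast against the arm that leaves sooner, provided that discharge timing differs by arm and scores are still falling at discharge. The first condition is one the trial itself hypothesizes; on the second the article is silent. The planned secondary analyses do not cure it.

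Over the assumed range (mean stay one or two days shorter, falls of 0.5 to 2 points per day, discharge unrelated to score) the artefact is +0.14 to +1.00 points on the 39-point scale. It is close to nil for discharge near the floor or flat scores afterwards. None of these figures is an estimate for this trial.

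A reader might infer that the artefact is likely to stop the trial for harm. The boundaries do not support that: a false crossing is very unlikely at the first look and becomes more plausible at the later ones, and the board makes a recommendation rather than applying an automatic rule.

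Apart from the size of the bias, the endpoint time differs between Background and Data Analysis, and the severity and duration rules disagree for patients discharged with delirium.

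**What to change.** 1. Settle one endpoint time, day 8 or the earlier of day 8 and discharge, and word the hypothesis and the Data Analysis section alike.
2. State one assumption about delirium after live discharge and apply it to both primaries, including patients discharged with delirium.
3. Make the day-8 contrast from the planned mixed-effects model, adjusted for baseline score, the primary severity analysis for live discharges, and use it at the harm looks too. A continuing trajectory sits closer than a frozen score to the plan's own assumption that days after discharge are free of delirium.
4. Keep carry-forward and the worst-score rule as sensitivity analyses.
5. State explicitly how deaths before day 8 enter the severity analysis, so that the mixed model does not silently project scores for patients who have died.

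This needs no new data and mainly swaps the roles of two analyses already planned. The cost is reliance on a missing-at-random assumption after discharge, which the observed data cannot verify. The retained analyses probe it: carry-forward represents no change after discharge, and the worst-score rule represents a poor course for those discharged with delirium.

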### Randomization

Following the eligibility and screening assessments, informed consent will be obtained from the participant's legally authorized representative. Randomization of eligible patients providing consent will occur in a 1:1 ratio between intervention and usual care groups. The computerized order entry system (GOPHER) is capable of performing this process and will conduct randomization in random blocks of four to encourage even distribution of patients between the intervention and usual care groups.

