#### Secondary Outcomes

The study will collect demographic and baseline functional information from the patient's legally authorized representative and/or caregivers. Cognitive function status will be obtained by interviewing the patient's legally authorized representative using the Informant Questionnaire on Cognitive Decline in the Elderly (IQCODE). IQCODE is a questionnaire that can be completed by a relative or other caregiver to determine whether that person has declined in cognitive functioning. The IQCODE lists 26 everyday situations where a person has to use their memory or intelligence. Each situation is rated by the informant for amount of change over the previous 10 years, using a Likert scale ranging from 1-much improved to 5-much worse. The IQCODE has a sensitivity between 69% to 100% and specificity of 80% to 96% for dementia [41].

Utilizing the electronic medical record system (RMRS), we will collect several data points of interest at baseline and throughout the study period. First, RMRS will allow us to collect reason for admission, severity of illness (APACHE II) [42], and the number of comorbid conditions (Charlson Comobidity Index) [43] for each patient enrolled in the study. We will also collect length of stay (both ICU and total hospital stay), mortality rate, and hospital-related consequences. We have previously defined hospital-related consequences to include: the number of patients with documented falls, use of physical restraints, injuries such as pulling out IV lines or urinary catheters, any ordered or observed re-intubation, and pressure ulcers. These will be assessed using the RMRS, direct daily observation, and retrospective review of the electronic medical record. This definition of delirium-related hospital complications has been previously used and published [44,45].

Use of all medications, including focused intervention-related medications (anticholinergics, benzodiazepines, and haloperidol) will be monitored through the GOPHER computerized order entry system, as well as the McKesson medication administration system. The McKesson system is used at the patient's bedside and collects the administration of each medication. Additionally, McKesson is able to monitor medications administered as continuous infusions by documenting start times, stop times, and drip rates throughout the administration period.

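### The lead test of delirium duration is unadjusted although plausible prognostic baseline variables are already collected: a valid choice that gives up some precision

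*Protocol article*

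**What the plan says.** The Data Analysis section of the protocol article takes the two primary outcomes in turn.

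- **Severity** (day-8 DRS-R-98): the primary analysis is "analysis-of-covariance (ANCOVA) with the baseline score as a covariate".
- **Duration**: the outcome is "the number of coma-free and delirium-free days in the first 8 days post-randomization". The arms are compared "using a two-sample t-test corroborated with the Wilcoxon rank sum test". The next sentence adds: "The intervention effect will be further tested while controlling for patient characteristics using multiple regression". No covariates are named.

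The article does not attach the word primary to the t-test. The order of the sentences, and the description of the regression as a further test, nevertheless put the t-test in the lead, with the Wilcoxon test as its check.

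Several baseline variables are already in hand. Under Secondary Outcomes, "RMRS will allow us to collect reason for admission, severity of illness (APACHE II) [42], and the number of comorbid conditions", together with demographics, baseline function and the IQCODE. A baseline DRS-R-98 score is implied by the severity ANCOVA, and ICU type is known from the eligibility criteria.

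**The concern.** The duration outcome runs from 0 to 8 days. Days after death count as not free of delirium or coma, and days after discharge count as free. Anything that predicts death or early discharge therefore plausibly predicts the outcome. Table 1 points the same way for ICU type: ICU mortality is 11% (SICU) and 12% (MICU + CCU) against 1.3% (PICU), and mean ICU stay is 5.96 and 6.10 days against 3.72. The table covers all ICU patients and not delirious enrollees, so it is only indicative.

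An unadjusted test leaves this between-patient variation in its standard error. Chance imbalance between the arms is part of the same loss and should not be counted a second time. At stake is power for one of the two primary outcomes, in a trial whose Discussion mentions small effects in earlier delirium trials and possible contamination between arms.

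**Working it through.** **Inputs from the article.** There are 428 evaluable patients ("after the completion of 0.25, 0.5 and 0.75 of the projected 428 evaluable subjects"). Allocation is equal ("Randomization of eligible patients providing consent will occur in a 1:1 ratio between intervention and usual care groups"), so 428 / 2 = 214 per arm. The overall alpha is 0.05 ("for an overall significance level of 0.05 at study completion").

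**Assumptions.** The test is two-sided (the article does not say). The benchmark effect is the one for which the t-test has 80% power. R² is the share of variance in free days explained by the baseline covariates. The article gives no R², so a range is shown.

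**The plan's own figure.** The sample size of 428 cannot be reproduced, because the article states no effect, SD or power. That is acceptable in a condensed article and is not raised here.

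**Unadjusted benchmark.** In SD units, the standard error of the difference is √(2/214) = 0.0967. The detectable difference at 80% power is (1.960 + 0.842) × 0.0967 = 0.271 SD.

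**Adjusted.** The standard error is multiplied by √(1 − R²), so:

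- detectable difference = 0.271 × √(1 − R²)
- power at 0.271 SD = Φ(2.802/√(1 − R²) − 1.960)
- equivalent unadjusted sample size = 428/(1 − R²)

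| Assumed R² | SE multiplier | Detectable difference (SD) | Power at 0.271 SD | Equivalent N |
|---|---|---|---|---|
| 0 | 1.000 | 0.271 | 80.0% | 428 |
| 0.02 | 0.990 | 0.268 | 80.8% | 437 |
| 0.05 | 0.975 | 0.264 | 82.0% | 451 |
| 0.10 | 0.949 | 0.257 | 84.0% | 476 |
| 0.20 | 0.894 | 0.242 | 88.0% | 535 |
| 0.30 | 0.837 | 0.227 | 91.8% | 611 |

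For an effect with 90% unadjusted power the same rows give 90.6%, 91.4%, 92.7%, 95.2% and 97.2%.

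**Cost of adjustment.** With k covariates the loss of degrees of freedom is recovered when R² is about k/(428 − 3): 4/425 = 0.009 for four covariates and 5/425 = 0.012 for five.

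**Check on a bounded outcome.** The calculation above treats the outcome as continuous. It was therefore simulated with 428 patients, values rounded and limited to 0–8, one normal baseline covariate and 3000 runs per setting. The simulated treatment effect differs between rows, so compare within a row.

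| R² (simulated) | t-test | Wilcoxon | Adjusted model |
|---|---|---|---|
| about 0.09 | 0.855 | 0.852 | 0.886 |
| about 0.18 | 0.820 | 0.818 | 0.899 |
| about 0.28 | 0.791 | 0.791 | 0.911 |

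With no treatment effect, rejection rates were 0.052/0.052/0.056 at R² of about 0.05 and 0.057/0.058/0.056 at about 0.10 (t-test/Wilcoxon/adjusted). The simulation standard error is √(0.05 × 0.95/3000) = 0.004. Adjustment did not inflate type I error relative to the t-test. The simulated model used ordinary and not robust standard errors.

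**The case against.** The strongest reply is that nothing here is wrong. A two-sample t-test is valid under 1:1 randomisation, an adjusted regression is already planned, and which of the two leads is a matter of preference. The covariate list is ordinary analysis-plan content. Severity has a baseline value of the same measure, which makes ANCOVA natural there; free days after randomization have no such counterpart. The gain depends on an R² that nobody has stated, and at 2% it is less than one percentage point of power.

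Most of this stands, and it limits the point to efficiency. The unnamed covariates are not a fault of the article, and the difference from the severity analysis is not an inconsistency. The argument about preference does not dispose of the matter, however. The article itself states the order of the tests, so that order is not left to an unseen document, and it decides which result counts if the t-test and the regression disagree.

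The reply also identifies a real cost. The three interim harm analyses use the primary analysis methods, the first after 0.25 × 428 = 107 patients. A change of primary method carries over to them.

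**Conclusion.** The point holds as an efficiency improvement. The plan leads with the less precise of two duration analyses that it already intends to run. On the stated assumptions the gain in power runs from about 1 point (R² 2%) to about 12 points (R² 30%). The direction is secure once R² exceeds about 1%; the size is not known.

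Several stronger readings are tempting, and the documents do not support them:

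- **The predictors are strong.** No correlation with free days is reported for any baseline variable; plausible is as far as the text goes.
- **The plan forgoes adjustment, or leaves the choice between t-test and Wilcoxon open.** It plans the regression, and it ranks the t-test above the Wilcoxon test.
- **Randomization is unstratified.** The Randomization section mentions blocks of four and is silent on strata. Silence in a condensed article does not settle this.
- **The trial is underpowered for duration.** Power at 428 cannot be checked from the article.

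**What to change.** Before unblinding, and preferably before the first interim harm analysis, state that the primary duration analysis is a linear regression of free days on treatment and a short list of named baseline covariates. The list would be baseline DRS-R-98 severity, age, APACHE II and ICU type, with IQCODE as an option. Use robust standard errors, because the outcome is bounded at 0 and 8. Keep the t-test and Wilcoxon test as supportive analyses.

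Two variables need care. CAM-ICU status should be left out: a positive result is an entry criterion, so it will hardly vary. Ventilation status is not in the list of baseline data under Secondary Outcomes and should be used only if it is recorded at randomization.

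The cost is a change of wording, with no extra patients and, for the four core covariates, no new measurements. The interim harm analyses would also have to use the adjusted model, so those covariates must be complete at each look (107, 214 and 321 patients).

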**Methods/Design:**

This is a randomized controlled trial of 428 patients aged 18 and older suffering from delirium and admitted to the ICU of Wishard Memorial Hospital in Indianapolis. Subjects assigned to the intervention group will receive a multicomponent pharmacological management protocol for delirium (PMD) and those assigned to the control group will receive no change in their usual ICU care. The primary outcomes of the trial are (1) delirium severity as measured by the Delirium Rating Scale revised-98 (DRS-R-98) and (2) delirium duration as determined by the Confusion Assessment Method for the ICU (CAM-ICU). The PMD protocol targets the three neurotransmitter systems thought to be compromised in delirious patients: dopamine, acetylcholine, and gamma-aminobutyric acid. The PMD protocol will target the reduction of anticholinergic medications and benzodiazepines, and introduce a low-dose of haloperidol at 0.5-1 mg for 7 days. The protocol will be delivered by a combination of computer (artificial intelligence) and pharmacist (human intelligence) decision support system to increase adherence to the PMD protocol.

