### Evaluation/Assessment Parameters

#### Primary Outcome

*Delirium Recognition: *In accordance with national guidelines [4], the study will identify delirium by using the RASS and the CAM-ICU on all patients who are admitted directly from the emergency room or transferred from other services to the ICU. Such assessment will be performed after 24 hours of ICU admission and twice daily until discharge from the hospital. As an initial step in conducting the CAM-ICU, the interviewer must assess the patient's sedation status to assure a valid CAM-ICU result. The CAM-ICU was validated using the RASS, and therefore this will be the sedation scale utilized for our study evaluation. RASS has excellent inter-rater reliability among adult medical and surgical ICU patients and has excellent validity when compared to a visual analogue scale and other selected sedation scales [28]. The RASS requires 30-60 seconds to perform with minimal training and has been used by our local ICU team. The RASS is a 10-point scale that reflects the patient level of sedation as determined by their responses to verbal versus physical stimulation. A RASS score of -5 indicates a comatose state with lack of response to verbal or physical stimuli, a score of 0 represents alert and calm, and a score of +4 indicates a state of combative, violent behavior with immediate danger to staff, self, or others. A patient with a RASS score of -3 to +4 will be considered eligible to be assessed by the CAM-ICU to determine the presence of delirium [29].

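### The duration outcome counts all post-discharge days as delirium-free, even for patients who leave delirious, and no sensitivity analysis tests this rule

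*Protocol article*

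**What the plan says.** The Data Analysis section of the protocol article compares "the number of coma-free and delirium-free days in the first 8 days post-randomization using a two-sample t-test corroborated with the Wilcoxon rank sum test", followed by a multiple regression that controls for patient characteristics. Two rules fill the days that are not observed. For deaths: "Patients who die before day 8 will have all subsequent days counted as not coma-free or delirium-free". For discharges: "We will impute all days post-discharge as coma-free and delirium-free". The discharge rule is unconditional, and no alternative to it is named.

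The same section treats severity differently. Its main analysis carries the last observed DRS-R-98 score forward to day 8. One of its sensitivity analyses assigns the worst recorded score "for patients who have been discharged with delirium or died before day 8".

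The Primary Outcome section ends the twice-daily CAM-ICU and RASS assessments at hospital discharge, so every credited day is unobserved. The Background section states as a secondary hypothesis that "the study intervention will result in (1) shorter hospital lengths of stay".

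**The concern.** The article expects some patients to leave hospital delirious and treats them as still ill when it analyses severity. When it analyses duration, it gives the same patients a clean record from discharge to day 8. A patient discharged delirious on day 3 is credited with days 4 to 8, which is 5 of the 8 days.

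The credit need not balance between arms. The article hopes that the intervention shortens stay, and order alerts and a study pharmacist make the arm visible to clinicians. If earlier discharge means that more patients leave before delirium has cleared, more delirious days are hidden in the intervention arm and are counted there as free. The Wilcoxon test and the regression use the same imputed count, so agreement among the three analyses would not reveal the problem. A positive duration result could then not be told apart from a change in discharge timing.

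**Working it through.** **Inputs from the article.** 428 patients randomised 1:1, so 214 per arm; an 8-day window; overall significance level 0.05, taken here as two-sided because sidedness is not stated. Mean ICU stay is 5.96, 6.10 and 3.72 days (SICU, MICU + CCU, PICU), and 12%, 14% and 38% leave the ICU for home or another facility (Table 1). Discharge inside the window is therefore plausible. Table 1 describes all ICU admissions, not delirious patients.

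**Not given.** The rate of discharge with delirium, the SD of the day count, and the effect size and power behind 428. The article attaches no figure to this rule, so there is none to reproduce. Everything below rests on assumed values shown as ranges.

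**Detectable difference.** (1.96 + 0.84) × √(2/214) = 2.80 × 0.0967 = 0.27 SD at 80% power. For SDs of 2, 2.5 and 3 days this is 0.54, 0.68 and 0.81 days.

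**Bias by arithmetic.** Let p be the proportion of an arm discharged delirious before day 8, and m the mean number of truly delirious days per such patient that are credited as free. If the delirium course is the same in both arms:

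bias = p(intervention) × m(intervention) − p(control) × m(control)

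With the same m in both arms this is Δp × m. The chance of a significant result favouring the intervention is Φ(bias / (SD × 0.0967) − 1.96), which is 2.5% when the bias is zero.

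| Δp | m (days) | Bias (days) | False benefit, SD 2 / 2.5 / 3 |
|---|---|---|---|
| 5 points | 3 | 0.15 | 12% / 9% / 8% |
| 10 points | 2 | 0.20 | 18% / 13% / 10% |
| 10 points | 4 | 0.40 | 54% / 38% / 28% |
| 15 points | 4 | 0.60 | 87% / 70% / 54% |

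The rows with m = 4 are the severe end. In the first simulation below, m works out at about 2.2 days (0.36 / 0.16).

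**Simulation 1: the rate of discharge while delirious differs.** Delirium duration is geometric with mean 4 days, identical in both arms; 214 per arm; t-test at two-sided 0.05, counting significance in either direction (5% expected).

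| Discharged delirious, control v intervention | Article's rule | True status | Status carried forward |
|---|---|---|---|
| 0% v 0%, intervention discharged faster | −0.01 days (5%) | −0.01 (5%) | −0.01 (5%) |
| 10% v 10% | 0.00 (5%) | 0.00 (5%) | 0.00 (5%) |
| 10% v 19% | +0.20 (15%) | 0.00 (6%) | −0.27 (18%) |
| 10% v 26% | +0.36 (39%) | −0.01 (5%) | −0.53 (51%) |
| 16% v 29% | +0.30 (29%) | −0.01 (6%) | −0.43 (34%) |

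In the 10% v 10% row the arms do not differ, but free days are overstated in both (4.62 against a true 4.40).

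**Simulation 2: the intervention arm's whole discharge distribution moves earlier.** Same delirium model, discharge times independent of delirium, and 5-13% of controls leaving delirious before day 8.

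- One day earlier: +0.08 to +0.18 days; false benefit 5-13%.
- Two days earlier: +0.19 to +0.41 days; false benefit 13-53%.
- Carrying discharge status forward instead, over the same scenarios: −0.11 to −0.62 days; false harm 7-62%.

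**The case against.** **The hypothesis concerns hospital days.** The Background section predicts "fewer hospital days with delirium or coma", and counting no delirium after discharge fits that wording. The rule is also prespecified, the same for both arms, and paired with an unfavourable rule for death. This has force, and it is a reason to leave the rule in place as primary. It does not remove the need for a check. The analysis is presented as a test of delirium duration over a fixed 8-day window, and a rule applied equally still favours the arm in which it hides more delirious days.

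**A reader might infer that earlier discharge by itself creates a benefit.** The documents do not support that. Discharge after lasting resolution changes nothing, as the first row of simulation 1 shows. The hypothesis of shorter stay comes alongside a hypothesis of less delirium, and nothing in the article predicts more delirious discharges. If discharge usually follows clearing of delirium, the bias shrinks towards zero. Simulation 2 assumes no such link.

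**A reader might also conclude that carrying status forward should replace the primary rule.** It should not. It is biased the other way, by a similar or larger amount. The interim analyses for harm use the primary analysis methods, so a swap would bring false harm into the monitoring.

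**A reader might suspect a second gap.** The Primary Outcome section labels RASS −5 comatose and says "A patient with a RASS score of -3 to +4 will be considered eligible to be assessed by the CAM-ICU", which leaves RASS −4 unplaced. Nothing says that such a day counts as free, and day-level scoring is commonly left to a full protocol or analysis plan. That is no finding.

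**Conclusion.** The point holds in a limited form. The article fixes an unconditional favourable imputation on a primary outcome and foresees the patients for whom it is wrong. It tests their handling for severity but not for duration. The result is an apparent benefit only if delirious days hidden by discharge are more numerous in the intervention arm.

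Under the assumptions of simulation 2, the bias is about +0.1 to +0.4 days and the one-sided false-benefit rate about 5-50% instead of 2.5%. The upper end needs a stay two days shorter with no effect on delirium. Against a detectable difference of 0.54 to 0.81 days, the bias runs from minor to a substantial share of the effect the trial could detect. Where it falls depends on a discharge rate that the documents do not give.

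**What to change.** 1. Keep the stated rule as the primary analysis.
2. Prespecify a sensitivity analysis for duration: where the last CAM-ICU/RASS assessment before discharge was positive (delirious or comatose), carry that status forward to day 8.
3. Report by arm the number discharged delirious or comatose before day 8.
4. Describe a duration benefit as robust only if its direction and conclusion hold under both rules.

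**Cost.** A few sentences of analysis text, one further analysis and one line in a table. The assessments are already made twice daily until hospital discharge, so no new data are needed, and the primary endpoint and interim monitoring are unchanged.

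**Downside.** The carried-forward rule is pessimistic for patients who clear soon after leaving and errs in the opposite direction. The two results bracket the truth and neither is unbiased. If many patients leave delirious, the bracket may be too wide to support a claim, and the counts by arm will show whether that is so.
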